#### 8.4 Randomisation

Random allocation to the three trial conditions (iCT, Mind-Online, standard practice) will be at a 1:1:1 ratio, stratified by site and initial eligibility (above or below cut-off on PHQ-9 and PCL-5 at screening) by the Oxford Clinical Trials Research Unit (OCTRU).

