### 11.2 The Number of Participants

We plan to recruit 570 participants.

The risk of student paramedics developing full syndromal PTSD and MD over two years without intervention is 10% (1), and 25% if subsyndromal PTSD and MD that cause significant distress are included. We predict that our intervention will reduce the relative risk by 50%. Setting power at 80%,  $\alpha=.05$  and hypothesizing a reduction of relative risk of 50% gives an odds ratio of 0.429, which requires a total sample size of N=304 to show a risk reduction of 50% between the active and placebo intervention. Thus, each condition would require N=152. Since we have a third condition (no-training control), the total sample size required would be N=456. Allowing for a 20% rate of attrition, we will require a total sample size of N=570.

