## **BACKGROUND AND OBJECTIVES**

### **Background and rationale**

Emergency workers are at risk for major depression (MD) and posttraumatic stress disorder (PTSD), and an associated risk of poor physical health due to the nature of their work.[1] To date, interventions aimed at reducing risk of mental ill health in this population have been unsuccessful. Randomised controlled trials (RCT) found that trauma risk management, a peer support system widely available to the police and ambulance services in England, [2] critical incident stress debriefing widely used by UK fire-services, [3] and the charity Mind's six-session group-based resilience intervention had no effect on resilience or rates of mental ill health [4]. More effective preventative interventions for emergency workers are urgently needed.

Established interventions may have been unsuccessful because they fail to target predictors of mental ill health and are offered to emergency workers after rather than before repeated exposure to the stresses linked to their work. Moreover, cognitive strategies that could help them cope with characteristic stressors are not included as part of the training. For example, our and others' research has demonstrated that exposure to trauma or stressful scenarios through imagery reduces anxiety for police officers and other at risk populations. [5, 6] Development of more effective interventions requires identification of predictors of mental disorders and an understanding of how to modify them.

In a series of experimental and prospective studies, we identified two cognitive factors that are robust predictors of poor mental health in emergency workers: rumination (repetitive negative thinking) and resilience appraisals. Those who reported ruminative thoughts during critical incidents were more likely to experience poor levels of coping. [7] Adaptive appraisals during analogue trauma led to more successful attempts to regulate

emotions and fewer PTSD symptoms. [8] Our large-scale prospective study of newly recruited paramedics investigated predictors of PTSD and MD derived from cognitive theories of PTSD and depression. [1] Rumination at the start of paramedic training uniquely predicted PTSD; low resilience uniquely predicted an episode of MD.

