## **STATISTICAL PRINCIPLES**

### **Statistical Significance and Multiple Testing**

In the case of different scaling, continuous variables are standardized for the analysis. Global comparisons are tested and if significant, group comparisons are then carried out.

[name], [name], [name], [name], [name], [name], [name], [name], [name], [name], [name], & [name] Cognitive resilience training to prevent PTSD and MDD in paramedics: A randomised controlled trial.

If not specified otherwise, one or the other, main effects of intervention group or interaction effects between intervention group and time in favour of iCT-R, indicate intervention superiority.

All analyses will be carried out with a significance level of  $p < .05$ , two-sided.

No adjustments for multiple testing are made, as the primary trial objective is to evaluate any superiority in efficacy of the new resilience intervention compared to the existing online intervention (group comparison between these two groups of highest priority and directive hypothesis).

Confidence intervals are reported at the 95% level, two-sided.

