## **Analysis Methods**

Analyses of the primary trial objectives:

To analyse any differences between the intervention arms in terms of effectiveness with regards to rates of PTSD and MDD diagnoses (SCID-5) at 1-year follow-up (short-term primary outcome time point) and at 2-years follow-up (long-term primary outcome time point once completed), intervention condition and the interaction between intervention time and

intervention group on rates of PTSD and MDD diagnoses, logistic mixed effects models with PTSD and MDD diagnoses as outcomes (short-term outcome 1-year follow-up data, long-term outcome 2-years follow-up once completed) are specified and analysed.

To analyse any differences between the intervention arms in terms of effectiveness with regards to PTSD symptom severity (PCL-5) or MDD symptom severity (PHQ-9) at 1-year follow-up (short-term primary outcome time point) and at 2-years follow-up (long-term primary outcome time point once completed), intervention condition (categorical; iCT-R versus Mind-Online versus Standard practice; level 2) and the interaction between intervention time (categorical; post-intervention, 6-months follow-up; 1-year-follow-up, 2-year follow-up, once completed; level 1) and intervention group on PTSD or MDD symptom severity, linear mixed effects models with either PTSD or MDD symptom severity as outcomes are specified and analysed.

Both repeated assessments and intervention arm are specified as categorical variables for reasons of flexibility in the modelling approach. Repeated assessments/ time, intervention arm, both their interaction effects, and baseline scores and covariates are estimated as fixed effects and random effects are estimated for time (level 1) nested within the participants (level 2). An unstructured variance-covariance matrix is used to model the error correlation structure within the participants. Estimation method is Maximum Likelihood. Normality of the residuals for the outcomes is confirmed visually.

Randomisation has been done by stratification by site, gender, and baseline PTSD symptom severity and MDD symptom severity. Therefore, baseline PTSD symptom severity and MDD symptom severity and randomisation factors are added as covariates in these models. Site is added as random factor in those models. If non-significant, they will not be carried forward into further analyses.

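### The primary diagnosis models do not adjust for baseline rumination and resilience, which the sponsor's own study found predictive: a small missed gain in power, not an error or a bias

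*Combined protocol and SAP*

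**What the plan says.** The SAP, under Analysis Methods, specifies logistic mixed models for the SCID-5 diagnoses of PTSD and MDD and linear mixed models for PCL-5 and PHQ-9. For these models, "baseline PTSD symptom severity and MDD symptom severity and randomisation factors are added as covariates in these models"; site is a random factor. The randomisation factors, under Randomisation and Blinding, are site, gender and cut-offs on baseline PHQ-9 and PCL-5. The Statistical Analysis Outline mentions covariates in general but names no others.

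The background sections of both documents describe the sponsor's prospective study of newly recruited paramedics. In the SAP's words, "Rumination at the start of paramedic training uniquely predicted PTSD; low resilience uniquely predicted an episode of MD". Protocol Appendix B schedules RRS brooding, RIQ, CD-RISC and the Wagnild scale at baseline.

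The SAP uses these constructs elsewhere. They are secondary outcomes, each adjusted for its own baseline, and their pre-to-post change is a predictor within the iCT-R arm. They could reach a diagnosis model by a stated route only through the sensitivity analysis that adds covariates predictive of missing data, and only if they turn out to predict missingness.

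**The concern.** The sponsor's evidence singles out two baseline traits as predictors of the two primary diagnoses. They are the traits that iCT-R is designed to change, and randomisation is not stratified on them. If they carry information beyond baseline symptom scores, adjusting for them raises the chance of detecting a real effect. It also removes the effect of a chance imbalance in traits that any reader of the results would ask about.

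Timing matters. The SAP (Timing of Final Analysis) quotes 1-year rates for the total sample only and states an intention to analyse. On the documents, covariates can therefore still be fixed before the arms are compared. Added afterwards, they would look chosen for their effect on the result.

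**Working it through.** **1. The plan's own sample size.** Inputs from protocol 11.2: a control risk of "25% if subsyndromal PTSD and MD that cause significant distress are included", halved to 12.5%, which "gives an odds ratio of 0.429"; power 80%. Tests are two-sided at 0.05 (SAP, Statistical Significance and Multiple Testing).

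OR = (0.125/0.875)/(0.25/0.75) = 0.429.

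n per arm = [1.96·√(2·0.1875·0.8125) + 0.8416·√(0.25·0.75 + 0.125·0.875)]² / 0.125² = (1.082 + 0.459)²/0.015625 ≈ 152.

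Then 2 × 152 = 304, 3 × 152 = 456, and 456/0.8 = 570. All stated figures reproduce from an unadjusted comparison, so the sample size does not rely on covariate adjustment.

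**2. What is not in the documents.** They give no effect size for rumination or resilience beyond baseline PCL-5 and PHQ-9. I assumed a log OR of 0 to 0.7 per SD for each, a baseline-severity OR of about 2.0 per SD and correlations of 0.4 to 0.5. The simulations use two arms of 152 and logistic regression at one time point, with severity in both models and no site or participant random effects. The Monte Carlo error of one power near 85% with 4,000 runs is √(0.85·0.15/4000) ≈ 0.6 points. Differences between models fitted to the same trials are more precise.

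**3. Both scores added, only one prognostic** (one predictor per disorder, as the sponsor's finding reads; 5,000 runs). Power without → with:

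| Risks | log OR 0.3 | 0.5 | 0.7 |
|---|---|---|---|
| 25% v 12.5% | 84.2 → 84.5 | 85.0 → 85.9 | 84.7 → 86.4 |
| 15.8% v 7.9% | 59.2 → 59.4 | 59.9 → 60.9 | 60.2 → 62.5 |
| 11.6% v 5.8% | 44.9 → 45.0 | 44.6 → 45.8 | 45.0 → 46.6 |

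The second row takes the pooled 1-year depression rate as the control risk. The third row averages to the pooled PTSD rate: (11.6 + 5.8)/2 = 8.7. The gain is about 0 to 2 points throughout.

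**4. Both scores added, both prognostic** (4,000 runs):

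| Risks | log OR 0 | 0.3 | 0.5 | 0.7 |
|---|---|---|---|---|
| 25% v 12.5% | 84 → 84 | 85 → 86 | 86 → 89 | 88 → 91 |
| 15.8% v 7.9% | 59 → 59 | 61 → 62 | 61 → 63 | 64 → 68 |

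The gain reaches about 4 points at most, and nothing material is lost if the scores add no information. Type I error with both covariates was 5.6% and 4.8% (log OR 0.5 and 0.7).

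**5. Where the gain comes from.** With one extra covariate at OR 2.0 per SD and 25% v 12.5%, the median SE of the treatment log OR rose from 0.335 to 0.347, while the log OR moved from −0.977 to −1.037. The ratio goes from 0.977/0.335 = 2.92 to 1.037/0.347 = 2.99. Power rises because the conditional estimate moves further from zero than its SE grows. In the linear PCL-5 and PHQ-9 models the mechanism is the usual one: residual variance falls by the share that the extra scores explain, so the SE itself shrinks. That share cannot be sized from the documents.

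**6. Chance imbalance.** I looked at the fifth of simulated trials in which iCT-R happened to receive the more ruminative, less resilient participants, with both scores prognostic at log OR 0.3, 0.5 and 0.7. At 25% v 12.5%, power went from 79 to 84%, 80 to 89% and 80 to 91%. This is a conditional view; averaged over all trials, the gain is the one in step 4.

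**7. Events available at 1 year.** PTSD: 456 × 0.087 ≈ 40 to 570 × 0.087 ≈ 50. Depression: 456 × 0.158 ≈ 72 to 570 × 0.158 ≈ 90.

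**The case against.** The plan already adjusts for both baseline severity scores and the stratification factors, which is a standard, pre-specified choice. Randomisation protects against bias, and chance imbalance in an unadjusted trait does not invalidate the test. This stands: the omission is neither an error nor a bias.

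A reader might infer that free precision is being thrown away. For the primary binary outcome that is not so, because the SE of the log OR rises. Only the linear models gain precision directly.

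A reader might also take the two traits as strong predictors and expect a gain equal to a sizeable increase in sample size. The documents do not support this. They do not say whether the earlier study adjusted for baseline symptoms, so the increment could be nil, and they tie one trait to each disorder. In addition, 25% is a two-year risk that includes subsyndromal cases, whereas the models concern diagnoses.

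The limit on parameters is real. With two post-baseline time points, arm (2), time (1), arm by time (2), PCL-5, PHQ-9, gender and two score strata already make about 10 fixed effects for 40 to 50 one-year PTSD cases. There are also rival instruments (RIQ, Wagnild), and the documents do not say which the earlier study used. These points limit how many scores to add. They do not argue against naming one of each in advance.

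**Conclusion.** The point holds as an inexpensive optional improvement. Two baseline traits that the sponsor's own study calls unique predictors are measured but not named in the primary diagnosis models. Under the assumed log OR of 0 to 0.7 per SD beyond symptoms and 152 per arm, the loss is about 0 to 2 power points if one predictor matters per disorder and up to about 4 if both do, at 25% v 12.5% or 15.8% v 7.9%. At the 8.7% PTSD rate it is about 0 to 2 points. These sizes rest on assumptions and on a simplified single-time-point model.

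Adjustment would not repair low power. By the unadjusted formula, 152 per arm gives about 57% at 15.8% v 7.9% and 38% at 10% v 5%, and a few points do not change that picture.

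**What to change.** Before the 1-year arms are compared, add to the SAP's Analysis Methods that baseline RRS brooding and baseline CD-RISC enter the PTSD and MDD diagnosis models and the PCL-5 and PHQ-9 models as continuous fixed covariates. State that they stay in whatever their p-values, because that section also carries a rule for dropping non-significant terms. Give a simple rule for missing baseline scores that uses neither arm nor outcome, for example the pooled baseline mean. If parameters must be limited because of the few PTSD cases, use rumination in the PTSD model and resilience in the MDD model.

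The cost is a few lines of SAP text and one or two extra parameters per model. No new data are needed.

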| Primary Objectives

1. Is internet-delivered cognitive training for resilience (iCT-R) more effective than accessing already available mental health information (Mind-Online) or having no specific training (standard practice), i.e., does iCT-R lead to fewer cases of PTSD and Major Depression (including subsyndromal PTSD and MD) and less PTSD and MD symptomatology at follow-up compared to Mind-Online and standard practice?                                    | 1.
Depression: PHQ-9 
PTSD: PCL-5 
Structured Clinical Interview for DSM-5 – PTSD and MD modules                                                                                                                                                                                                                                                                                                                                                                                                                                                                               | 1.
Baseline
6 weeks
52 weeks
104 weeks          |
| Secondary Objectives

1. Does internet-delivered cognitive training for resilience (iCT-R) lead to greater improvement in secondary outcome measures (resilience, rumination, hormone and immune function, smoking, weight gain, alcohol use, symptoms of anxiety, and sleep problems, psychological distress, wellbeing) than Mind-Online and standard practice?

2. Is iCT-R more cost-effective than Mind-Online or standard practice, i.e., is the cost per | 1.
Resilience: CD-RISC  , Wagnild & Young 
Rumination: RRS  (Brooding) & RIQ 
Anxiety: GAD-7 
Smoking & Alcohol Use: Smoking & Alcohol Use (unpublished)
Weight: Weight Questionnaire (unpublished)
Sleep problems: ISI 
Psychological distress: General Health Questionnaire (GHQ-12) 
Wellbeing: WEMWBS 
Hormone function: cortisol levels
Immune function: CRP levels

2.
Quality of life: EQ-5D-5L 
Costs: Trimbos/iMTA-TiC-P  , Client | 1.
Baseline
6 weeks
52 weeks
104 weeks          |

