#### **Description of Compliance with Intervention**

Level of compliance will be defined as 1) number of online modules completed during the intervention, 2) practice of tools.

A complier-average causal effect analysis (CACE) is used to test any influence of compliance on the intent-to-treat intervention effect of the primary trial objective analyses.

1067

1068

1069 **Reliability**

1070           The primary outcome measures, such as Structured Interviews by clinicians and self-  
1071 reports for the primary outcomes and nearly all of the secondary outcome measures are  
1072 standard instruments that have been validated and have shown good reliability.

1073           Scoring is done as described in the manuals or publications for the measures and  
1074 relevant sub-scales and Cronbach's Alphas are reported for the study sample.

1075           Interrater-reliability is reported for 1-year follow-up data. 10% of diagnoses at 1-year  
1076 follow-up are rated by a second rater.

1077           To ensure consistency in the data, validation checks on the data are carried out before  
1078 locking the dataset and analysis of the data. These include checking for potential data entry  
1079 mistakes, duplicate records, checking the range of variable values, missing data value codes,  
1080 etc.

1081 **ANALYSIS**

1082 **Outcome Definitions**

1083 Outcome measures:

1084           The primary outcome measure for the primary trial objective is PTSD and MDD  
1085 diagnoses (SCID-5;). Secondary outcomes with regards to the primary trial objective are  
1086 PTSD symptom severity (PCL-5) and MDD symptom severity (PHQ-9).

1087

1088           Outcome measures for the secondary trial objectives include resilience measures  
1089 (Wagnild-Resilience Scale and CD-RISC, both continuous), well-being measures (subscale  
1090 rumination of the RIQ, GAD-7, GHQ-12, WEMWBS), general health measures (weight and  
1091 height; Insomnia severity index; Smoking Behaviour Questionnaire, sum score for both  
1092 items; Alcohol Use Questionnaire, unit increase/ decrease/ stayed the same), health economic  
1093 costs (intervention costs per QALY gained based on 4 measures), and hormone and immune  
1094 function (collected with saliva samples and CRP plasma).

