In case of a significant main effect of intervention group or interaction effect between intervention group and time with regards to the primary outcome measure (PTSD and MDD diagnoses) and secondary outcome measures for the primary trial objective (PTSD and MDD symptom severity), intervention group comparisons are carried out using pairwise contrasts. iCT-R (coded as '1') is tested against Mind-Online (coded as '0') and a significant main effect or interaction in favour of iCT-R indicates intervention superiority (comparison of highest priority) of the newly developed resilience intervention over the existing online intervention. In a second step, iCT-R (coded as '1') is then tested against Standard Practice

(coded as '0') and again, a significant main effect or interaction in favour of iCT-R indicates intervention superiority for the newly developed intervention over usual Standard Practice. In a third step, Mind-Online (coded as '1') is tested against Standard Practice (coded as '0') and a significant main effect or interaction in favour of Mind-Online indicates intervention superiority of the existing online intervention compared to Standard Practice.

Adjusted/ estimated mean differences and Cohen's d's with standard deviation at baseline in the denominator are reported in tables for continuous outcomes for the intervention effects from results of linear mixed effects models and frequencies of diagnoses (absolute numbers and percentages) and absolute values as well as estimated/ adjusted odds ratios are reported for dichotomous outcomes.

All significance tests are carried out on a  $p < .05$  level, two-sided, and confidence intervals are reported on the 95% level.

Analyses of secondary trial objectives:

Any intervention effects on the secondary outcome measures, such as resilience (Connor-Davidson Resilience Scale,; Wagnild Resilience Scale), rumination (ruminative responses brooding subscale; Responses to Intrusions Questionnaire rumination subscale), anxiety (GAD-7), Smoking Behaviour (Smoking Behaviour Questionnaire), Alcohol consumption (Alcohol Use Questionnaire), psychological distress (GHQ), well-being (Warwick Edinburgh Mental Wellbeing Scale), sleep quality (Insomnia severity index), and weight, are analysed for the short-term primary outcome time point of 1-year and for the long-term primary outcome time point of 2-years follow-up, once completed.

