## Main trial analyses and Covid:

Descriptive statistics for the two outcome measures for the primary trial objectives (PTSD and MDD diagnoses and PTSD or MDD symptom severity) are reported for the whole sample and by intervention groups based on the Covid grouping variables for the short-term primary outcome time point at 1-year follow-up and the 2-year follow-up assessment point, once completed (means and standard deviations for continuous outcomes and absolute numbers and percentages for diagnoses).

In the case of any differences, additional analyses are carried out to explore whether there is any possible intervention heterogeneity depending on participants' Covid status on PTSD and MDD diagnoses or PTSD and MDD symptom severity at 1-year follow-up or at 2-year follow-up, once completed. In this case, linear and logistic mixed models are specified in the same way as proposed for the analyses of the primary trial objectives and participants' Covid status variables are entered as exogenous time-varying covariates. Two-way interaction terms between those covariates and intervention group as well as three-way interaction terms between Covid status, time, and intervention group are analysed. In the case of significant interaction terms, which could possibly indicate intervention heterogeneity, additional effect size measures are reported. Adjusted mean differences and Cohen's  $d$ 's with standard deviation at baseline in the denominator are reported in tables for continuous outcomes from results of linear mixed effects models and frequencies of diagnoses (absolute numbers and percentages) and absolute differences as well as odds ratios are reported for dichotomous outcomes.

In addition to Covid status depending on time points, the COVID questionnaire, scored as a continuous variable, which assesses the self-reported impact of COVID on a participant will be descriptively reported and analysed as a covariate in a similar way like the time-based covariates to determine whether or not it influences outcome. We will compare rates of PTSD and MDD for the sample who score positive on the item ('I am graduating

early as a result to support the NHS workforce') compared to participants who do not endorse this item.

Exploration of missing data patterns and possibly additional sensitivity analyses:

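### The SAP ranks diagnoses above PCL-5 and PHQ-9, but one superiority rule covers them all with no test order across outcomes, so the ranking does not limit what may be claimed

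*Combined protocol and SAP*

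**What the plan says.** **Protocol.** The Primary row of the Synopsis and the Primary Objectives row of section 5 list the SCID-5 modules, PCL-5 and PHQ-9 together, without a rank. The primary question asks about fewer cases "and less PTSD and MD symptomatology at follow-up compared to Mind-Online and standard practice", so symptom level is part of it.

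**SAP, ranking.** SAP 2.2 words the primary objective in terms of diagnoses only, and SAP 3.7 names diagnoses as the primary outcome measures. SAP 6.1 says: "The primary outcome measure for the primary trial objective is PTSD and MDD" diagnoses on the SCID-5. It then says: "Secondary outcomes with regards to the primary trial objective are" PCL-5 and PHQ-9 severity.

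**SAP, looser wording.** SAP 5.6 opens with "The primary outcome measures, such as Structured Interviews by clinicians and self" and goes on to include self-reports. SAP 6.6 refers to "Descriptive statistics for the two outcome measures for the primary trial objectives (PTSD and MDD diagnoses and PTSD or MDD symptom severity" without ranking them.

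**SAP, decision rule.** SAP 6.2 models diagnoses and scales under the primary trial objectives. Its rule for going on to arm comparisons is stated "with regards to the primary outcome measure (PTSD and MDD diagnoses) and secondary outcome measures for the primary trial objective (PTSD and MDD symptom severity". For either set, a significant main effect or interaction favouring iCT-R counts as superiority. SAP 4.1 sets two-sided .05 throughout and adds: "No adjustments for multiple testing are made". The reason given is that iCT-R versus Mind-Online is the comparison of highest priority.

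**The concern.** A ranking protects the error rate only if it governs what may be claimed. Here it attaches labels, and the superiority rule then ignores them. The SAP's reason for not adjusting concerns the choice of arms and says nothing about the number of outcomes.

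Suppose the diagnoses show no difference and PHQ-9 does. That result meets the superiority rule in the primary-objective analysis, and the protocol's list would support presenting it as primary. The prevention question, and the event rate that the sample size rests on, concern cases. SAP 3.2 has interviews done by blinded assessors, whereas the scales are completed by participants who, it says, cannot be fully blinded. The two kinds of evidence are not interchangeable.

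**Working it through.** **1. The plan's own figure.** Protocol 11.2 and SAP 3.3 size one binary comparison. Inputs: 25% versus 12.5% (a 50% relative reduction), two-sided .05, 80% power. With mean proportion 0.1875 and pooled variance under the null:

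n = [1.960·√(2·0.1875·0.8125) + 0.842·√(0.25·0.75 + 0.125·0.875)]² / 0.125² = 151.9, so 152 per arm.

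OR = (0.125/0.875)/(0.25/0.75) = 0.429. Then 2 × 152 = 304, 3 × 152 = 456, and 456/0.8 = 570. The figure reproduces, and it covers one test of one endpoint.

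**2. What is controlled.**

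| Device in the SAP | Acts on | Acts across outcomes? |
|---|---|---|
| Global three-arm test before arm comparisons (3.7, 4.1, 6.2) | each outcome separately | no |
| Order of the three arm comparisons (3.7, 6.2) | each outcome separately | no |
| Reason for no adjustment (4.1) | choice of arms | no |
| Primary and secondary labels (6.1, 6.2) | names of outcomes | no condition attached |

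**3. Size.** Simulation assuming no true differences, with three equal arms and k outcomes whose standardised arm means have common correlation ρ. The documents give no correlation, so ρ is assumed. For each outcome the global test is a 2-df chi-square at .05. If it is significant, iCT-R versus Mind-Online is tested at |z| > 1.96. One effect per outcome; 4,000,000 draws per setting. Entries are for ρ = 0 / 0.5 / 0.8.

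| Outcomes | At least one significant global test | False iCT-R vs Mind-Online difference, two-sided | Same, favouring iCT-R |
|---|---|---|---|
| 1 | 5.0% | 2.5% | 1.2% |
| 3 (composite diagnosis, PCL-5, PHQ-9) | 14.3 / 12.7 / 10.0% | 7.3 / 6.6 / 5.2% | 3.7 / 3.3 / 2.6% |
| 4 (two diagnoses, PCL-5, PHQ-9) | 18.5 / 15.8 / 11.7% | 9.6 / 8.3 / 6.1% | 4.9 / 4.1 / 3.1% |

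Check at ρ = 0: 1 − 0.95⁴ = 18.5%, and 1 − (1 − 0.025)⁴ = 9.6%.

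**4. The either-effect rule.** SAP 4.1 lets a main effect or an interaction establish superiority. Treating these as two independent tests (an assumption), false superiority of iCT-R on at least one of four outcomes is 9.6% (ρ = 0), 8.2% (0.5) and 5.9% (0.8), against 2.5% for one outcome.

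**5. Why the count is three or four.** No composite of PTSD and MDD is defined, and SAP 3.5 reports the rates separately (8.7% and 15.8%). The sample size nevertheless uses one combined rate. Both counts are therefore shown.

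**The case against.** The strongest answer is that the SAP ranks the outcomes repeatedly: SAP 2.2, 3.7, 6.1 and 6.2 all put diagnoses first, and the sensitivity analyses (6.4) and subgroup analysis (6.5) concern diagnoses only. Under the SAP alone, a PHQ-9-only result is secondary. That stands. A reader might infer that the SAP treats the scales as co-primary, and it does not. The SAP 6.6 wording fits the category of secondary outcomes under the primary objective, and SAP 5.6 is a loose phrase in a reliability paragraph. The real conflict is between protocol and SAP. What the answer does not supply is any consequence of the ranking for a claim.

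A reader might also infer that four tests at .05 give 18.5% to 11.4% false iCT-R versus Mind-Online differences. Those figures leave out the global test that the SAP requires first. They would be approached only if both programmes truly beat Standard Practice on every outcome by enough to make the global test almost sure to be significant. The documents do not assume this; SAP 3.3 describes Mind-Online as having shown no change in PTSD or MDD rates.

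Expectation effects should not be overstated either. Protocol 9.2 and SAP 3.1 give Mind-Online six modules and the same frequency, type and duration of support, which limits differential expectation in the priority comparison. The worry is greater against Standard Practice.

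**Conclusion.** The point holds as a gap in the decision rule. The SAP's ranking is explicit but has no effect on claims, and it departs from the protocol's list without saying so. A symptom-scale result alone meets the superiority rule under the primary objective.

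The inflation is moderate. For iCT-R versus Mind-Online across four outcomes, a false difference is about 2.4 to 3.8 times as likely as with one outcome (6.1/2.5 to 9.6/2.5). In favour of iCT-R, the rate exceeds 2.5% in every three- and four-outcome setting shown, though narrowly with three outcomes at ρ = 0.8 (2.6%). These figures assume no true differences, ρ between 0 and 0.8, and one effect per outcome at one time point. The main-effect-or-interaction rule adds to them, as in step 4, and so would counting both the 1-year and 2-year analyses.

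**What to change.** In SAP 6.1 and 6.2:

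- State that only the SCID-5 diagnoses decide the primary objective.
- Say whether they form one combined PTSD-or-MDD endpoint, in line with the single rate in the sample size, or two endpoints tested with Holm. Without this, two diagnoses at .05 each stay unadjusted: the chance of at least one significant global test is 1 − 0.95² = 9.75% if independent.
- Test PCL-5 and then PHQ-9 for a claim, in that stated order, only if the diagnosis result is significant. Otherwise report estimates with 95% confidence intervals and no superiority wording.
- State that this ranking replaces the protocol's unranked list, and align the wording of SAP 5.6.

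The cost is wording, plus one real restriction: a symptom-scale result alone can no longer be called superiority on the primary objective. A combined endpoint followed by a fixed sequence holds .05 across outcomes and leaves N = 570 unchanged on the plan's own 25% rate. If two endpoints are kept, the first Holm step at .025 lowers power at 152 per arm from 80.0% to 71.1%, even at 25% versus 12.5%. Splitting alpha equally over four outcomes (.0125 each) would lower it to 61.7%, so a test order is the cheaper route.
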